**Fig. 1 Fig1:**
[figure not shown]
Overall treatment schedule GnG-Study. Abbreviations: DA, daunorubicin; low-dose cytarabine; GO, gemtuzumab ozogamicin; HiDAC, high-dose cytarabine (1 g/m^2^); MRD, measurable residual disease; CR, complete remission; CRi, CR with incomplete hematological recovery. In case of bone marrow blast count > 10% or no CR/CRi after on day 15 after induction therapy one cycle of HAM (high-dose cytarabine and mitoxantrone) is allowed. Maintenance is intended in all patients in CR/CRi irrespective of completion of consolidation therapy

Glasdegib and placebo are interrupted in patients experiencing adverse events of grade 3 or 4. Appropriate follow-up assessments are performed until adequate recovery from toxicity. In patients recovering within 21 days from dose interruption, glasdegib/placebo may be resumed. If hematological recovery parameters are not met after 21 days of dose interruption, permanent discontinuation of treatment with glasdegib/placebo is advised. Criteria for dose interruption and dose reductions in cases of non-hematological toxicities including applicable doses in milligrams are summarized in Tables 1 and 2.

**Table 1 Tab1:** Glasdegib interruptions in case of toxicities

Toxicity causing glasdegib interruption	Resumption within the first 21 days when:
Any toxicity grade ≥3 according to CTCAE criteria potentially attributable to glasdegib regardless of when it occurs in the cycle.	Toxicity returns to patient’s baseline/ toxicity resolved (non-hematological toxicity recovers to grade ≤1)
ANC < 0.1G/l and /or platelets <10G/l regardless of when it occurs in the cycle	ANC ≥0.1G/l and platelet count ≥10G/l and re-treatment can occur safely as per the investigator’s judgment
No resolution of above toxicities after 21 days	Discontinue medication permanently

Glasdegib doses omitted for toxicity are not replaced within that cycle (e.g., cycles are not to be prolonged beyond 28 days in order to make up for any missed glasdegib doses during that cycle). Toxicity is graded according to CTCAE criteria. Once the Glasdegib dose has been reduced, all subsequent cycles should be administered at that dose level, unless further dose reduction is required. Dose re-escalation is not allowed. Abbreviations: *CTCAE* Common Terminology Criteria for Adverse Events, *ANC* absolute neutrophil count.

**Table 2 Tab2:** Glasdegib dose reduction in case of non-hematological toxicities

Toxicity	Glasdegib dosage modification
Non-hematologic toxicities grade ≥3 according to CTCAE criteria (excluding QTc prolongation, muscle spasms, and myalgias). First episode Second episode Third episode	Interrupt medication until toxicity recovers to grade ≤1, then: Dose level decrease 1 (DLD1): 75 mg DLD2: 50 mg Discontinue medication permanently
Renal toxicity, where serum creatinine or BUN are ≥2 × ULN or serum bicarbonate level is < 20 mmol/L. First episode Second episode Third episode	Interrupt medication until toxicity recovers tograde ≤1 then: DLD1 DLD2 Discontinue medication permanently
Electrocardiogram QT corrected (QTc) prolongation grade 1.	Continue at the same level.
QTc prolongation grade 2 and 3.	Interrupt and resume when QTc returns to ≤470 ms: - Within 7 days, dosing as before - Within 14 days, DLD1 Discontinue medication permanently, in case of no return to ≤470 ms after 14 days,
QTc prolongation grade 4 or repetitive grade 3 or grade 2 after DLD1.	Discontinue medication permanently

Toxicity is graded according to CTCAE criteria. Once the Glasdegib dose has been reduced, all subsequent cycles should be administered at that dose level, unless further dose reduction is required. Dose re-escalation is not allowed. Nausea, vomiting, or diarrhea must persist until next therapy cycle at grade ≥3 to require dose modification

Abbreviations: *CTCAE* Common Terminology Criteria for Adverse Events, *QTc* QT corrected, *DLD1* dose level decrease 1: 75 mg, *DLD2* dose level decrease 2: 50 mg, *ULN* upper limit normal

#### Long-term follow-up

The period of observation under therapy ends with the last visit of the sixth cycle of maintenance therapy. After the end of treatment visit, patients are routinely followed-up according to standard of care. Follow-up is intended until the last patient alive has been observed for at least 2 years (study treatment including subsequent follow-up). Assuming 2 years of linear recruitment, total observation of the first patient may last up to 4 years and a median follow-up of 3 years at end of study is expected.

Event-free survival and OS observational follow-up are recorded until the end of the study. After achieving an observation period of 2 years counted from day 1, the follow-up may be performed by contacting the treating physician instead of in house-visits.

#### Additional study procedures during induction, consolidation, and continuation phases

Patients undergo efficacy and safety assessments, including monitoring of MRD, bone marrow specimen collection, blood and urine sampling, and patient-reported outcomes before receiving study drug and at specified time points throughout the study (supplementary Tables 1 to 4).

### Participants

#### Inclusion criteria

Inclusion criteria are outlined in Table 3. Key inclusion criteria are newly diagnosed AML according to the 2016 WHO classification, no prior chemotherapy for leukemia except hydroxyurea for up to 7 days to control hyperleukocytosis, age 60 years and older, and ECOG PS between 0 and 2.

**Table 3 Tab3:** Inclusion and exclusion criteria

Category	Inclusion	Exclusion
Population characteristics	- Patients with newly diagnosed acute myeloid leukemia according to the 2016 WHO classification. - Genetic and immunophenotypic assessment in one of the central laboratories. - Age ≥ 60 years, no upper age limit. - ECOG performance status ≤2. - Effective contraception method.	- AML with PML-RARA or BCR-ABL1. - Patients with known active CNS leukemia. - Pregnancy and lactation. - Known or suspected active alcohol or drug abuse. - Known positivity for HIV, active HBV, HCV, or hepatitis A infection. - Severe neurologic or psychiatric disorder interfering with ability of giving informed consent.
Prior therapies	- No prior chemotherapy for leukemia except hydroxyurea to control hyperleukocytosis (≤7 days).	- Prior treatment with a smoothened inhibitor (SMOi) and/or hypomethylating agent.
Comorbidities		- Inadequate renal function. - Inadequate liver function. - Known liver cirrhosis. - History of sinusoidal. Obstruction syndrome. - Uncontrolled hypertension. - Severe obstructive restrictive. ventilation disorder. - Myocardial infarction. - Congenital long QT syndrome. - Torsades de pointes. - Arrhythmias (including sustained ventricular tachyarrhythmia). - Right or left bundle branch block and bifascicular block. - Unstable angina. - Coronary/peripheral artery bypass graft. - Symptomatic congestive heart failure (NYHA III/IV). - Cerebrovascular accident. - Transient ischemic attack. - Symptomatic pulmonary. embolism. - Bradycardia defined as < 50 bpms. - QTc interval > 470 msec. - Uncontrolled infection. - Evidence or history of severe non-leukemia associated bleeding diathesis or coagulopathy. - Patients with a “currently active” second malignancy other than non-melanoma skin cancer.
Others	- Signed written informed consent. - Ability of the patient to understand character and consequences of the clinical trial.	- No consent for biobanking. - History of hypersensitivity to the investigational medicinal product or to any drug with a similar chemical structure. - Participation in a clinical study involving an investigational drug.

Abbreviations: *AML* acute myeloid leukemia, *CNS* central nervous system, *ECOG* Eastern Cooperative Oncology Group, *NYHA* New York Heart Association

#### Exclusion criteria

Exclusion criteria are summarized in Table 3. Main exclusion criteria are diagnosis of acute promyelocytic leukemia (APL) with translocation t(15;17)(q22;q12) or *BCR-ABL*-positive AML. Other exclusion criteria are known active CNS leukemia, HIV, viral hepatitis, prior treatment with a smoothened inhibitor (SMOi) and/or hypomethylating agent, as well as known liver cirrhosis or history of SOS.

### Efficacy

The GnG trial has two efficacy endpoints. The first is MRD-negativity after sequential or single-dose GO in combination with intensive induction therapy. MRD-negativity is defined as the absence of leukemic cells at the end of the induction therapy assessed by flow cytometry with a sensitivity of 10^-4-^10^-5^. If MRD-negativity cannot be measured, or if patients drop out of the study before MRD measurements, missing values will be replace using multiple imputation. Patients who die from any cause before MRD measurement will be regarded as MRD-positive. The second endpoint is EFS after two years; EFS is defined as the time from randomization until one of the following events, whichever occurs first: a) failure to obtain CR or CR with incomplete neutrophil or platelet recovery (CRi) after induction therapy, b) relapse from CR/CRi or c) death from any cause. Patients without an event are censored at last follow-up. Refractory disease or treatment failure is defined as failure to achieve CR or CRi, presence of Auer rods, or appearance of new or worsening extramedullary disease after induction therapy. Relapse after CR or CRi is characterized by ≥5% blast cells in the bone marrow aspirate and/or biopsy not attributable to any other cause, the reappearance of leukemic blasts in the peripheral blood, appearance of extramedullary leukemia, or presence of Auer rods. Platelet (≥100 G/l) and neutrophil (≥1.0 G/l) counts for the assessments of CR and CRi are assessed according to standard criteria [4].

Secondary survival endpoints are OS (defined as time from randomization until death from any cause) and relapse-free survival (RFS) (measured from first CR/CRi to time of recurrence of the disease or death from any cause, whichever occurs first). Patients without an event are censored at the last date of follow-up. Further secondary endpoints are response (CR/CRi) after induction therapy, patient-reported outcomes (PROs) and pharmacoeconomics. PROs include assessments of a) health-related quality of life (QoL), calculated as the EORTC QLQ-C30 Summary Score [34], b) the quality of sleep or sleep disorders, calculated with the “Sleep Quality Index” from the PSQI according to the corresponding scoring guidelines [35], and c) anxiety and depression, calculated from the PHQ-4 according to the corresponding scoring manual [36]; pharmacoeconomics with health care resource utilization is assessed by self-administered resource utilization questionnaire and the SF-36 [37] [38] questionnaires for health economic analyses with patient-reported information on personal traits and experiences are collected at baseline.

### Safety assessments

All adverse events (AEs) that occur after the clinical screening visit (or as soon as the medical history of the patient has been examined) are documented. The period of observation ends with the last study visit. All patients who have AEs, whether considered associated with the use of the investigational medical products or not, are monitored for outcome determination. All AEs are coded using the latest version of the Medical Dictionary for Regulatory Activities and assigned grades based on National Cancer Institute Common Terminology Criteria for Adverse Events, version 5.00. The Data Monitoring Committee (DMC) reviews all data relevant to safety. The DMC, which is composed of three independent experts meets regularly and provides the sponsor with recommendations regarding trial modification, continuation, or termination.

### Auditing

Audits are planned to be performed based on the regular risk-based evaluation. Regulatory authorities and auditors authorized by the sponsor may request access to all source documents, the CRF, and other trial documentation. Investigators are contractually bound to enable direct access to these documents and to support audit activities.

### Protocol amendments

Decisions regarding protocol amendments will be taken by the study core team encompassing the coordinating investigator, trial coordinator, trial statistician, medical coordinator, and data management. Meetings for reviewing all available findings and information are scheduled every 2 weeks.

### Data collection and handling

All data required as per the study protocol, including clinical and laboratory data, are documented by the investigator or an authorized member of the study team in the medical record of the patient and in the eCRF. Access to the eCRF is password protected and an audit trail is in place. Any entries are tracked and locked to prevent further editing. The investigator at the clinical site is responsible for ensuring that all sections of the eCRF are completed correctly. Entries are checked for plausibility and consistency via eCRF-inherent edit checks and visually by the monitors where necessary. Implausibility and missing entries are queried and to be clarified with the responsible investigator. All relevant documents and data collected within the study will be archived for at least 10 years after the termination of the study.

### Study Monitoring

Study monitoring is done by the Heidelberg Clinical Studies Coordination Center (KKS). A total of 130 monitoring visits to 25 study sites (5 per site on average) are planned over a study period of 48 months. The first monitoring visit at each study center is scheduled to occur at the end of the second patient's induction therapy. Further monitoring visits at each study site will depend on the (i) recruitment of study participants, (ii) the monitor's assessment of the trial site’s compliance with applicable stipulations (e.g., number and severity of protocol deviations or deficiencies detected during study visits), (iii) the deficiencies detected in the Central Data Review, and (iv) the assessment of the coordinating team. The monitoring is carried out according to a monitoring manual giving comprehensive guidance on monitoring activities (SDV rules, corrective and preventive actions, documentation of protocol violations, escalation of findings etc.).

### Ancillary and post trial care

The treatment period (EOT) ends after the last visit of the sixth cycle of maintenance therapy or may end prematurely for various reasons. After EOT patients are routinely followed up and treated as per the standard of care at the discretion of the treating physician. The period of observation ends for all patients when the last patient being included and alive has been followed for at least 730 days (2 years) counted from this patient’s day 1 of study treatment.

### Ethical and legal aspects

Before the start of the trial, the trial protocol, informed consent document, and any other appropriate documents were submitted to the independent Ethics Committee (EC) as well as to the competent federal authority (BfArM). A written favorable vote of the EC and an approval by the competent higher federal authority are a prerequisite for initiation of the clinical trial. All the procedures set out in this trial protocol are designed to ensure that all persons involved in the trial abide by Good Clinical Practice (GCP) and the ethical principles described in the current version of the Declaration of Helsinki. The trial is carried out in keeping with local legal and regulatory requirements. Before being admitted to the clinical trial, all patients must consent in written form to participate after the nature, scope, and possible consequences of the clinical trial have been understood by the patient.

All planned substantial changes to the study (protocol amendments) are to be submitted in writing to the EC and the competent federal authority requesting their approval. . Records of relevant communication with the EC and the regulatory authorities are kept by the coordinating investigator.

### Access to data and dissemination policy

After the publication of the complete trial, access to selected raw data is intended. This must be done in accordance with the European data protection act and informed consent given by the patients.

The results from this trial will be presented at national (e.g., annual meeting of the German Society of Hematology/Oncology); meetings of the Competence Net “Acute and Chronic Leukemias” and international meetings (e.g., meetings of the European Leukemia-Net; annual congresses of the European Hematology Association, the American Society of Hematology and the American Society of Clinical Oncology). The full results will be published in high-impact peer-reviewed medical journals.

### Sample size calculation and statistics

Addressing two primary endpoints, MRD-negativity after induction therapy and EFS, 252 evaluable patients are needed to reject each of the two null hypotheses at a two-sided significance level of 2.5% with a power of at least 85%.

The first primary endpoint evaluation involves the comparison of rates of MRD-negativity assessed by flow-cytometry after induction therapy between GO-147 and GO-1. Assuming a rate of MRD-negativity of 45% for GO-147 and 20% for GO-1, as well as a 3% dropout rate, a total number of 252 evaluable patients are needed to reject the null hypothesis of no difference regarding the MRD-negativity rate for patients receiving GO-147 as compared to patients receiving GO-1 during induction therapy at a two-sided significance level of 2.5% with a power of at least 85% using a chi-squared test.

The second primary endpoint evaluation involves a two-group comparison of EFS between the experimental arm of glasdegib as well as the control arm of placebo both as adjunct to standard consolidation therapy. Assuming a 2-year EFS of 38.5% for the experimental arm and a 2-year EFS of 21% for the control arm (resulting in a hazard ratio of HR=0.612), as well as an exponentially distributed dropout rate of 5% at 2 years, a total number of 224 evaluable patients (based on a number of *d*=178 required events) are needed to reject the null hypothesis assuming no difference regarding EFS for patients receiving glasdegib as compared to patients receiving placebo at a two-sided significance level of 2.5% with a power of at least 85% using a log-rank test, assuming an accrual time of 24 months, as well as a follow-up time of 24 months. This leads to a total sample size of N=max(252, 224)=252 patients to be enrolled for the whole trial to ensure a power of at least 85% for both primary endpoints.

The MRD-negativity after induction therapy is analyzed using a generalized linear mixed model and EFS with a Cox regression frailty model. Both models are adjusted for the following fixed factors: treatment (MRD-negativity: GO-1 vs. GO-147 and EFS: glasdegib vs. placebo), age, sex, and ECOG PS, as well as for the random factor “recruiting center”. The primary analysis is based on the full analysis set including all randomized patients. Adjustment for multiple testing is done using the Bonferroni-Holm procedure in order to control the family-wise error rate at a two-sided significance level of 5% in the strong sense. Missing values for the short-term primary endpoint MRD-negativity are replaced using multiple imputation by using the fully conditional specification method [39]. Odds and hazard ratios are reported alongside with two-sided 97.5% and 95% confidence intervals, and a possible center effect is assessed by calculating the intra-class correlation coefficient and by presenting the results stratified for the center. A sensitivity analysis of the long-term primary endpoint additionally includes the interaction between maintenance therapy and induction therapy. Statistical analysis is performed using SAS v9.4 or higher.

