**Methods/Design:**

This is a randomized phase III trial with measurable residual disease (MRD) after induction therapy and event-free survival (EFS) as primary endpoints. The two research questions are addressed in a 2 by 2 factorial design. Patients age 60 years and older are upfront randomized 1:1 in one of the two induction arms: GO administered to intensive induction therapy on days 1,4, and 7 versus GO administered once on day 1 (GO-147 versus GO-1), and double-blinded 1:1 in one of the subsequent treatment arms glasdegib vs. placebo as adjunct to consolidation therapy and as single-agent maintenance therapy for six months. Chemotherapy backbone for induction therapy consists of standard 7 + 3 schedule with cytarabine 200 mg/m^2^ continuously days 1 to 7, daunorubicin 60 mg/m^2^ days 1, 2, and 3 and high-dose cytarabine (1 g/m^2^, bi-daily, days 1, 2, and 3) for consolidation therapy. Addressing two primary endpoints, MRD-negativity after induction therapy and event-free survival (EFS), 252 evaluable patients are needed to reject each of the two null hypotheses at a two-sided significance level of 2.5% with a power of at least 85%.

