### Study setting and randomization

In Germany, patients with newly diagnosed AML are usually referred to academic Hospitals. In this study, patients will be recruited in 25 academic centers registered in the Study Alliance Leukemia (SAL) group. Participating centers are contacted by study monitors and the medical coordinator monthly to promote patient recruitment. Furthermore, after protocol amendments or upon relevant updates during the study, a newsletter will be sent to all participating centers. Conferences with the participating centers of the SAL network are done regularly to share information regarding therapy responses and complications seen within the study. Expecting at least 5 eligible patients per year and center, approximately 2 years are required to recruit the intended number of patients.

Each patient having signed informed consent and meeting all inclusion criteria is registered in the electronic case report form (eCRF). Via eCRF a unique patient ID (PAT-ID) is assigned. Following registration, eligible patients are upfront randomized 1:1 to induction chemotherapy containing either fractionated GO treatment (GO-147) or one single dose of GO (GO-1) and again 1:1 either to glasdegib or placebo (double-blinded) as adjunct to consolidation therapy and as single-agent for 6-months of maintenance therapy. Following these randomizations, 63 patients shall be allocated to each arm. Randomization is stratified by assumingly important prognostic factors age (≤70 years vs. > 70 years) and Eastern Cooperative Oncology Group (ECOG) performance status (PS) (ECOG PS = 0 vs. ECOG PS > 0). Block randomization with varying block lengths is used and performed using the web tool www.randomizer.at, by which randomization for double-blind clinical trials can easily be handled. Patients withdrawn from the trial retain their identification codes. Patients have to provide written informed consent before any protocol-specific procedures are performed. Applicable regulatory requirements, Good Clinical Practice, and ethical principles from the Declaration of Helsinki are adhered to during the study.

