### Post-randomization events

If MRD-negativity cannot be measured, the outcome will be imputed. Any-cause death before MRD measurement, will be regarded as MRD-positive. Dropouts (including lost-to-follow-up) are considered as censoring events. The dropout rate for the assessment of the short-term endpoint is assumed to be 3%. For the long-term endpoint EFS, a dropout rate of 5% is expected 2 years after randomization. Dropout times are assumed to be exponentially distributed.

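### The MRD sample size of 252 does not follow from its printed inputs: 45% vs 20% needs about 153 patients, so the rates and the N that sets the trial size must be reconciled

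*Protocol article*

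**What the plan says.** All inputs for the MRD comparison stand in the protocol article under *Sample size calculation and statistics*. The rates and dropout are given as "Assuming a rate of MRD-negativity of 45% for GO-147 and 20% for GO-1, as well as a 3% dropout rate", and the error rates and test as "at a two-sided significance level of 2.5% with a power of at least 85% using a chi-squared test". The result is that "a total number of 252 evaluable patients are needed to reject the null hypothesis of no difference regarding the MRD-negativity rate".

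The second calculation in that section, for EFS, gives 224 patients and 178 events. The trial size is then the larger of the two: "This leads to a total sample size of N=max(252, 224)=252 patients to be enrolled for the whole trial".

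*Study setting and randomization* has 1:1 allocation for each question and four cells: "Following these randomizations, 63 patients shall be allocated to each arm", that is 4 x 63 = 252. The abstract (*Methods/Design*) repeats that "252 evaluable patients are needed to reject each of the two null hypotheses", without giving the MRD rates.

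**The concern.** A difference of 25 percentage points is large, and 126 patients per induction arm is far more than a chi-squared test needs to detect it with 85% power at two-sided 2.5%. The EFS calculation asks for only 224, so it is the MRD figure that sets the size of the trial. If that figure does not follow from its inputs, one of two things is true. Either the rates are right and MRD does not drive the trial at all, or the N is right and the published planning difference for a primary endpoint is wrong. In the second case a reader would misjudge what the MRD comparison was built to detect.

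**Working it through.** **Inputs** (all from *Sample size calculation and statistics*, allocation from *Study setting and randomization*): p1 = 0.45, p2 = 0.20, dropout 3%, alpha 2.5% two-sided so z = 2.241, power 85% so z = 1.036, chi-squared test, 1:1 allocation.

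**Step 1: MRD with the printed rates.** The usual pooled-variance formula per arm is

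n = [2.241·√(2·p̄(1−p̄)) + 1.036·√(p1(1−p1) + p2(1−p2))]² / (p1−p2)², with p̄ = 0.325.

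The two terms are 1.485 and 0.662, so n = (2.146)² / 0.0625 = 73.7, or 74 per arm. The total is 148, and 148/0.97 = 152.6, or 153. The plan's 252 is not reproduced.

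**Step 2: other versions of the test, same alpha and power.**

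| Version | Total before dropout | With 3% dropout |
|---|---|---|
| Pooled chi-squared | 148 | 153 |
| Unpooled variance | 142 | 147 |
| Arcsine | 146 | 151 |
| Continuity-corrected | 164 (82 per arm) | 170 |
| Fisher exact | slightly over 160 (160 gives 84.8% power, 168 gives 86.9%) | at most 174 (168/0.97) |

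None comes near 252. Counting the 3% dropouts as MRD-positive gives 156. Treating the comparison as 63 vs 63 within one glasdegib stratum gives 78% power, so that reading does not explain 252 either. Reaching about 252 with the printed rates takes power of about 97.5–98% at alpha 2.5%, or another alpha combined with 95–99% power. The article states none of these.

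**Step 3: the EFS calculation in the same section.** HR = ln(0.385)/ln(0.21) = 0.612. Events = 4·(2.241 + 1.036)²/(ln 0.612)² = 177.8, or 178. With exponential survival and dropout (5% at 2 years), 24 months of uniform accrual and 24 months of follow-up, the mean event probability is 0.801. Then 178/0.801 = 222.2, so 223 patients, or 224 as four equal cells. The EFS figures reproduce; the mismatch is confined to MRD.

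**Step 4: rates that do lead to 252.**

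- 45% vs 25%, pooled: 120.5, so 121 per arm, 242 in total; 242/0.97 = 249.5, or 250; four equal cells of 63 make 252.
- 40% vs 20%, continuity-corrected: 111.1 before and 120.9 after correction, so 121 per arm, and the same 242, 250 and 252.

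Both are differences of 20 points, not 25, and both need a final rounding to four equal cells that the article does not describe.

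**Step 5: power at N = 252 under the printed assumptions.** For MRD it is 98.1% with 126 per arm, and 97.7% with 122 per arm after 3% loss. For EFS, 252 x 0.801 = 202 expected events, which gives 89%.

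**Step 6: the article's own rule with the recomputed figure.** max(153, 224) = 224, so 252 − 224 = 28 patients, or 28/224 = 12.5%.

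**The case against.** The best defence is that the article promises power of at least 85% for both endpoints, and 252 delivers it: 98% and 89% under the printed assumptions. That stands. A reader might infer from the mismatch that the trial is underpowered, or that its power statement is false; the figures do not support either. What fails is narrower: the section says 252 are needed under these inputs, and then takes a maximum over required sizes.

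A second defence is that this is a condensed article and a rate may simply have been mistyped. That is plausible, but all inputs and the result are printed together and they disagree.

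Three stronger readings are also tempting.

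- *The GO-1 rate of 20% is the misprint and should be 25%.* This fits, but so does a GO-147 rate of 40% with a continuity-corrected test. The article cannot separate these from an error in the 252 itself.
- *The trial is 65% too large* (252 against 153). EFS independently requires 224, so the excess is at most 28 patients. If a rate was misprinted there may be no excess at all.
- *252 evaluable patients mean that 260 must be enrolled* (252/0.97). The 252 is derived with the dropout already included, is called the number to be enrolled, and equals 4 x 63 randomised. Inflating it again would count dropout twice. The word *evaluable* is a labelling slip, not a shortage.

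**Conclusion.** The point holds as an internal contradiction in the calculation that sets the trial size. With 45% vs 20%, 3% dropout, two-sided alpha 2.5%, 85% power and a chi-squared test, about 153 patients are needed (about 170 with continuity correction), not 252. This rests only on printed inputs, 1:1 allocation and dropout applied as N/(1−0.03), and no standard version of the test changes it. Which printed figure is wrong cannot be told from the article.

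The consequence is limited. Either the planning difference for MRD is misstated (25 points printed where 20 would fit), or EFS and not MRD sets the minimum, and N exceeds the article's own rule by 28. The validity of the analysis and the control of the type I error are not affected. It still has to be corrected, because it concerns the stated design effect of a primary endpoint and the figure from which N is taken.

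The finding is no ground for cutting enrolment to 224 before the rates are settled. If 45% vs 25% were the true planning rates, 112 per arm would give MRD power Φ[(0.20·√112 − 1.512)/√(0.2475 + 0.1875)] = Φ(0.917), about 82%, which is below the 85% target.

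**What to change.** Go back to the original sample size calculation and reconcile the MRD rates with the N. Then do one of the following in *Sample size calculation and statistics*:

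1. If other inputs were used, print the rates and the version of the chi-squared test that actually yield 252, including the rounding to four equal cells.
2. If 45% vs 20% is right, state that MRD needs about 153 patients, that EFS (224) sets the minimum, and that N = 252 gives about 98% power for MRD and about 89% for EFS. The abstract's statement that 252 are needed for each hypothesis would then have to be reworded too.

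In either case, as a minor point, describe 252 in that section and in the abstract as the randomised total including 3% dropout for MRD, instead of as evaluable patients.

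The cost is a check of the planning file and a change of wording. No patients are added, and the analysis and alpha stay as they are.
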